# Identification and transfer to stepped care of depressed and psychosocially stressed parents during peri- and postpartum—UPlusE: study protocol for cluster randomized trial of a screening intervention

**DOI:** 10.1186/s13063-024-08610-y

**Published:** 2024-11-14

**Keywords:** Postnatal depression, Psychosocial stress, Screening, Mental health, Infants, Cost-effectiveness, Regulatory problems, EPDS, PBQ, Utilization

## Abstract

**Background:**

Perinatal depression affects 10–15% of mothers and approximately 5% of fathers. However, only a small number of affected individuals seek treatment. If left unrecognized and untreated, it can have negative long-term consequences for the family’s health, leading to subsequent high costs. Early treatment is crucial, yet there is a notable underdiagnosis and undertreatment. Affected individuals are often seen during this time, e.g. in paediatric practices, but not by specialists in mental health. Consequently, this study aims to increase detection and treatment rates of affected individuals by implementing a screening for depression and psychosocial stress in perinatal and postpartum parents within routine obstetric and paediatric care with subsequent advice and—if necessary—further referral to a mental health specialist.

**Methods:**

UPlusE is a prospective, cluster-randomized controlled trial conducted in an outpatient setting. Obstetric and paediatric practices will be randomized into an intervention and control group (1:1 ratio). Practices and enrolling patients will be required to use specific smartphone apps (practice apps) for interaction. The screening will occur with the apps at each paediatric checkup up to the child’s age of 12 months, using the Edinburgh Postnatal Depression Scale (EPDS), KID-PROTEKT questionnaire, and the scale 1 (impaired bonding) of the Postpartum Bonding Questionnaire (PBQ-1). The goal is to screen 10,000 patients across Germany. Gynaecologists and paediatricians will receive certified training on peripartum depression. Participants in the intervention group with scores above cut-offs (EPDS ≥ 10, KID-PROTEKT ≥ 1, PBQ-1 ≥ 12) will receive counselling through their treating gynaecologists/paediatricians and will be provided with regional addresses for psychiatrists, psychotherapists, and “Frühe Hilfen” (early prevention) as well as family counselling centres, depending on symptom severity. At each screening, participants will be asked whether they sought support, where, and with whom (utilization). Utilization is the primary outcome.

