Participants from practices in the intervention group will receive the result of the screening and suitable recommendations for support whenever positively screened during the observation period: pregnant individuals enrolled in gynaecologic practices or parents enrolled in paediatric practices who screen positively during their initial contact with UPlusE will promptly receive the recommendations. Pregnant individuals/parents in the intervention group who are initially screened as negative but are subsequently screened as positive during the course will receive the recommendations from that point onward. As screening tools, the Edinburgh Postnatal Depression Scale (EPDS), the KID-PROTEKT questionnaire, and the scale 1 (impaired bonding) of the Postpartum Bonding Questionnaire (PBQ) will serve. The intervention flow is depicted in Fig. 2. For an EPDS score ≥ 13, trained physicians should encourage the affected parents to promptly consult a mental health practitioner in the region as provided through the app. In case of an EPDS score of 10–12, it is recommended that individuals consider seeking assistance from mental health professionals or, alternatively, ‘Early Prevention’ services. In case of a PBQ scale 1, score ≥ 12, and/or KID-PROTEKT questionnaire ≥ 1 and EPDS < 10, physicians encourage the affected individuals to seek support from ‘Early Prevention’ and other counselling services. The relevant regional addresses will be provided to participants of the intervention group through the apps and the UPlusE website (www.upluse.de). If needed, the physician will support them in making contact. Before each U-checkup, questionnaires are sent again via the app, and the utilization of support services is assessed. The app itself does not guide physicians in treatment recommendations but rather replaces paper questionnaires and calculators to make the screening process more efficient and sustainable.

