### Outcomes {12}

The primary and secondary endpoints, as well as the parameters of the process evaluation, are presented in Table 1 along with the time points for assessment and measurement methods.

**Table 1 Tab1:** Primary and secondary outcomes UPlusE evaluation

Primary endpoint	Measurement	Time points	Methods
Utilization of services from mental health practitioners/"Early Prevention"	Project-specific questionnaire	From inclusion to U6 checkup	Apps ‘My Paediatric Practice’, ‘My Gynaecology Practice’, all participating parents
Secondary endpoints			
Depression/severity of depression	EPDS (Edinburgh Postnatal Depression Scale)	From inclusion to U6 checkup	Apps (as above), all participating parents
Parent–child bonding	PBQ (Postpartum Bonding Questionnaire)	From inclusion to U6 checkup (child's age of 10–12 months)	Apps (as above), all participating parents
Psychosocial burden	KID-PROTEKT questionnaire	From inclusion to U6 checkup (child’s age of 10–12 months)	Apps (as above), all participating parents
Child regulation	Extended SFS questionnaire	From inclusion to U6 checkup (child’s age of 10–12 months)	Apps (as above), all participating parents
Stigmatization	Project-specific questionnaire	Inclusion and U6 checkup (child’s age of 10–12 months)	Apps (as above), all participating parents
Process evaluation, participant acceptance/satisfaction	Project-specific questionnaire	At U6 checkup (child’s age of 10–12 months)	Apps (as above), parents in the intervention group
Process evaluation, acceptance/satisfaction of participating practices	Project-specific questionnaire	After completion of implementation phase (months 33–35)	Apps (as above), all participating gynaecological and paediatric practices
Process evaluation, acceptance/satisfaction of mental health practitioners/ ‘Early Prevention’	Project-specific questionnaire	After completion of implementation phase (months 33–35)	All involved mental health practitioners/ ‘Early Prevention’ services
Utilization of services in the healthcare system	Analysis of data from the participating health insurance funds	After completion of implementation phase	Data from all participating parents and children
Healthcare system costs in the first year after childbirth	Analysis of data from the participating health insurance funds	After completion of implementation phase	Data from all participating parents and children

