‘quite often’, ‘sometimes’, ‘rarely’, and ‘never’) [27].5.Questionnaire on Crying, Feeding, and Sleeping (SFS):For measuring infant regulatory disorders, the extended SFS questionnaire will be used, comprising 37 items about infant crying, sleeping, and eating behaviour [28]. Total mean scores above 1.84 (crying and sleeping) or above 1.27 (feeding scale) indicate regulatory problems. Six items based on DC: 0–5 (classification system for the diagnosis of mental disorders in infants, toddlers, and preschool children) will be used for further differentiation and clinical classification of symptoms related to excessive crying, sleep disorders, and early childhood feeding disorders.6.Questionnaire on treatment/counselling utilization:Utilization of treatment for mental health issues and counselling for psycho-social stress and parent-child bonding issues will be systematically captured via a project-specific questionnaire in the practice apps ‘My Gynaecology Practice’ and ‘My Paediatric Practice’ through self-report by the participants. The questionnaire assesses information about whether treatment/counselling has been sought. If utilization has occurred since the previous assessment, details such as the institution visited (pregnancy counselling centre, child protection coordination centres, ‘Early Prevention’ services, specialized outpatient clinic, psychiatrist/psychosomatics/psychotherapist, general practitioner, other), the motivating factor, and the referrer will be collected. As of our knowledge, specifically fitting standardized, validated, and publicly published questionnaires for this purpose are currently not available.7.Process analysis questionnaireTo identify technical and organizational barriers as well as facilitating factors for the implementation of the care model, a process evaluation will be conducted. This involves surveying all participating practices, mental health practitioners, and counselling services. Except for mental health practitioners and ‘Early Prevention’, the survey will be conducted using project-specific questionnaires via the practice apps ‘My Gynaecology Practice’ or ‘My Paediatric Practice’. Mental health practitioners and ‘Early Prevention’ services cannot be reached through the practice apps: for the process evaluation, these recipients will be invited to participate in the survey via email by the responsible contact persons from the study team. The survey will use a digital form. The questionnaires for process evaluation will be designed by the Institute for Community Medicine, University Medicine Greifswald, and will cover aspects such as:The number of participating practices, mental health practitioners, and ‘Early Prevention’ services.Their reasons for participation.The feasibility of implementing the intervention in their respective settings.Acceptance of the intervention.Perceived technical and/or organizational barriers or gaps in the implementation of the intervention.Benefits perceived by the involved practices, mental health practitioners, and ‘Early Prevention’ services due to the intervention,Factors promoting the implementation of the care model.

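### The primary endpoint, utilization, is described in several ways that do not agree, and no rule stops a mere attempt or the enrolling practice's own counselling from counting

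*Protocol article*

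**What the plan says.** The protocol article describes the primary endpoint in several places.

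- **Abstract, Methods:** "participants will be asked whether they sought support, where, and with whom (utilization). Utilization is the primary outcome".
- **Objectives {7}:** the main research question concerns use of any support service by affected parents.
- **Outcomes {12}, Table 1:** the row begins "Utilization of services from mental health practitioners" and adds only Early Prevention.
- **Sample size {14}:** the 15% and 25% rates refer to use of mental health services.
- **Plans for assessment {18a}, item 6:** the lead statement is "The questionnaire assesses information about whether treatment/counselling has been sought". The next sentence begins "If utilization has occurred since the previous assessment, details such as the institution visited", and its list of institutions ends "specialized outpatient clinic, psychiatrist/psychosomatics/psychotherapist, general practitioner, other".
- **Additional analyses {20b}:** the per-protocol set is screen-positive parents who sought assistance.
- **Discussion:** with utilization as primary outcome, the trial is expected to show that more parents seek treatment or counselling.

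On the intervention side, the Abstract says that screen-positive parents in the intervention arm are counselled by their own gynaecologist or paediatrician. Intervention description {11a} adds: "If needed, the physician will support them in making contact". Section {17a} states that the trial is open, and item 6 of {18a} that utilization is self-reported.

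**The concern.** Seeking help and receiving it are different events, and the protocol treats them as different. The Abstract aims at higher treatment rates, and the secondary questions ask how quickly treatment starts and how long parents wait for appointments. A parent still on a waiting list at U6 has sought support but has not yet used it. Under some of the wordings this parent is a success, and under others not.

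The intervention also shares vocabulary with the endpoint. The practice counsels parents about psychosocial stress and bonding, and the questionnaire asks about counselling for psychosocial stress and bonding. A parent could honestly report the practice's own talk under *other*. Help with making contact is part of the intervention and could be reported as having sought support.

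If such reports were scored as events, delivery of the intervention would partly register as its own outcome, and mostly in one arm. This differs from recall or desirability bias, because it can arise with entirely truthful answers.

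**Working it through.** **1. Which events count under each wording**

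- *Attempt without an appointment:* counts under the Abstract, {20b} and the Discussion. Under Table 1, the Objectives and the sample-size text it does not count on a natural reading, since they speak of use. Item 6 of {18a} points both ways: its lead statement says sought, its follow-up says utilization that has occurred and an institution visited.
- *General practitioner only, or other only:* recorded by the questionnaire, and plausibly an event under the Objectives (any support service). Not an event under Table 1 as worded.
- *Early Prevention or counselling centre only:* an event under the Objectives; Early Prevention is also an event under Table 1. Doubtful under the sample-size text, which names mental health services only.
- *Talk with the enrolling practice:* named nowhere. Gynaecologist and paediatrician are not among the listed institutions, so it could enter only through *other*. No section excludes it.

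**2. The plan's own sample-size figure**

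Inputs from {14} and {20a}: 15% versus 25%, two-sided alpha 0.05, power 0.80, 1:1 allocation. With n per arm and p̄ the mean of the two rates,

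power ≈ Φ{[Δ − 1.96·√(2p̄(1−p̄)/n)] / √([p₁(1−p₁)+p₂(1−p₂)]/n)}.

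With n = 250, p̄ = 0.20 and Δ = 0.10: (0.10 − 1.96 × 0.0358)/0.0355 = 0.84, so power is 80%. The stated 500 is reproduced. Clustering and dropout give (500 × 1.725)/0.80 = 1078, as stated. Taking the plan's design effect at face value, 250 independent parents per arm is therefore the effective size.

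**3. Illustration of one-sided miscounting**

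Assumptions not in the documents: true use is 15% in both arms, there is no miscounting in the control arm, and some extra percentage points are counted in the intervention arm.

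- 3 extra points (15% vs 18%): (0.03 − 1.96 × 0.0332)/0.0332 = −1.06, so a significant result about 15% of the time. This needs 0.03/0.85 = 3.5% of intervention non-users to be miscounted.
- 5 extra points (15% vs 20%): (0.05 − 1.96 × 0.0340)/0.0339 = −0.49, so about 31%. This needs 0.05/0.85 = 5.9% of non-users.

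The nominal rate is 5%. A value of 10 extra points would merely restate the planned effect and is not used.

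**4. Illustration of equal miscounting**

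If 5% of non-users in both arms are counted and the true rates are 15% and 25%, the apparent rates are 0.15 + 0.85 × 0.05 = 19.25% and 0.25 + 0.75 × 0.05 = 28.75%, and power falls from 80% to 70%. At 10% the rates are 23.5% and 32.5%, and power is 61%. A loose event definition therefore costs something even when it does not favour an arm.

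**The case against.** A reader might infer that the plan actually counts failed contact attempts and the intervention's own talk as successes. The document does not support that reading.

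- Item 6 of {18a} makes the details conditional on utilization having occurred and asks for the institution visited. A parent on a waiting list has visited none. The Abstract may simply condense this.
- A response list is not an event definition. Table 1 names mental health practitioners and Early Prevention, so general practitioner and *other* can be recorded without being scored. Which list entries count may properly be settled in an analysis plan.
- The enrolling specialties are not on the list, and the referrer is recorded separately. For the practice's talk to count, a parent would have to report it as *other* and the analysts would have to score *other* as an event.
- The contrast is not confined to one arm. Under {11b}, control parents also receive a recommendation after a positive suicidality answer, a response from the physician when the child may be at risk, and encouragement to seek support when clinical signs appear.
- The miscounting rates are assumed, so the arithmetic shows sensitivity and not likelihood.

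All of this stands, and it limits the point to events that are not prevented from counting. It does not settle which wording governs. Nor can an analysis plan fully repair the matter: it can choose among institutions, but it cannot recover attendance if the app did not ask for it, or separate the practice's talk from other entries under *other*.

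**Conclusion.** The point holds as an inconsistency in the definition of the primary endpoint, with an open route to miscounting. The document uses sought support, any support service, mental health practitioner or Early Prevention, and mental health services for what is meant to be one outcome, and the planning rates are tied to the narrowest of these. The choice changes what a positive result would mean.

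That attempts or the practice's own counselling will be counted is not established; the text leaves it unresolved. The size of any bias cannot be derived from the documents. The figures of about 15% and 31% for 3 and 5 extra points rest on no true effect, a 15% rate in both arms, no miscounting in control, and 250 independent parents per arm. They show only that a small imbalance in counting would matter for an open, self-reported endpoint.

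**What to change.** State one primary event and use it in the Abstract, Objectives {7}, Table 1, Sample size {14} and item 6 of {18a}: at least one attended contact (in person, by phone or by video) after inclusion with a service in Table 1's classes. State that contacts with the enrolling gynaecological or paediatric practice do not count. Bring the wording in {20b} and the Discussion into line.

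Add one yes/no app item asking whether an appointment took place. Report parents who sought support without an appointment, and those with general practitioner or *other* contact only, as separate categories.

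The cost is one questionnaire item and some rewording. Event rates may be somewhat lower than under the looser wordings, so the 15% and 25% assumptions should be checked against the chosen event. Recruitment began in February 2024, so answers given before the change would have to be classified from the institution field. The change is therefore better made early.

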**Discussion:**

The screening is designed to reduce underdiagnosis to enable suitable support at an early stage (especially for those often overlooked, such as individuals with “high-functioning depression”) and hence to avoid manifestation of mental health problems in the whole family, especially infants who are exceptionally dependent on their parents and their well-being will benefit from this program.

**Trial registration:**

German Clinical Trials Register, DRKS00033385. Registered on 15 January 2024.

## Administrative information

Note: the numbers in curly brackets in this protocol refer to SPIRIT checklist item numbers. The order of the items has been modified to group similar items (see http://www.equator-network.org/reporting-guidelines/spirit-2013-statement-defining-standard-protocol-items-for-clinical-trials/).

Role of sponsor {5c}	The study sponsor initiated the study and is responsible for coordinating it. The funding body was not actively involved in the study design or will be in the data collection or analysis or interpretation or publication of the results.

## Introduction

### Background and rationale {6a}

A good start in life can be significantly compromised by a parent’s mental illness. Perinatal depression has a prevalence of 10–15% among mothers [1] and approximately 5% among fathers [2]. Psychosocial stressors (including depression) are reported by 30% of parents [3]. The prevalence of suicidal thoughts during pregnancy and postpartum ranges from 5 to 14% [4]. Suicide is one of the leading causes of death among mothers in the first year after childbirth [4]. However, significantly fewer individuals affected by a mental illness (like for example depression and anxiety disorders as the most common conditions) seek treatment during the perinatal period compared to other life phases [5]. Left unrecognized and untreated, both conditions can have negative long-term consequences for the family’s health and lead to high subsequent costs [6–8]. These illnesses often become chronic [9], resulting in impairments in sensitive caregiving for the child, attachment disorders, child regulatory problems, and, in the worst case, emotional neglect and abuse [10–12]. Early treatment of depression reduces individual suffering [1], enhances parenting skills [13], and reduces healthcare system costs [14–17]. Nevertheless, only a fraction of affected patients are diagnosed and treated early; due to lack of awareness and stigma, there is still a pronounced underdiagnosis and undertreatment [5, 18]. Gynaecologists and paediatricians regularly encounter individuals in this phase of life but frequently fail to recognize their psychological burdens [18]. For instance, there are highly functional affected individuals who appear capable and healthy, even though they are severely ill. Without a screening in routine care in these cases, mental illnesses often go unnoticed—with all the aforementioned risks. To reliably and promptly identify mothers and fathers with perinatal mental illnesses screening by gynaecologists and paediatricians is meaningful, feasible, and urgently needed [4, 14, 19–21]. So far, there are no general, systematic, and standardized early detection programs in Germany, and timely, low-threshold, and tailored provision of support is not organized. While the current guidelines for children and maternity care of the German Federal Joint Committee* (Kinder- und Mutterschafts-Richtlinien des* Gemeinsamen Bundesausschusses (G-BA)) partially consider the need to recognize psychosocial burdens, these risk factors are only identified in individual cases, as binding and feasible standards for required assessment are lacking so far. Hence, the identification of mental illnesses, such as depression, in pregnant women and parents is not yet a part of routine care. This aspect will be addressed by the G-BA-funded project “UPlusE (U-Untersuchung für Kinder PLUS Eltern beim Pädiater zur Förderung der kindlichen Entwicklung mit Impuls aus frauenärztlicher Schwangerenvorsorge”—Paediatric Check-up for Children PLUS Parents at the Paediatrician to Promote Child Development with Input from Gynaecological Prenatal Care). Within UPlusE, a systematic and very low-threshold screening for peripartum/postnatal depression or high psychosocial stress in (A) pregnant women during the third trimester by their treating gynaecologists and in (B) parents during paediatric checkups (so called U-checkups) for their children (up to U6-checkup at age of 10–12 months) by their treating paediatricians will be conducted throughout Germany. In the case of a positive screening result, the affected parents will be referred by their respective doctors for appropriate support (including psychiatry, psychotherapy, and psychosomatics treatments, hereafter referred to as “mental health specialists”) and/or to “early prevention” and family support programs (including early prevention services *Frühe Hilfen*, *pro familia*, and family and parenting counselling centres, pregnancy counselling centre, child protection coordination centres as well peer support groups).
